**Figure 3 F3:**
[figure not shown]
Flowchart of project.

### Statistical analysis

The Kolmogorov-Smirnov test will be used to test the data with regard to Gaussian distribution. Central tendency and dispersion measures will be expressed as mean and standard deviation values or median and inter-quartile interval when exhibiting parametric and non-parametric distribution, respectively. Either repeated-measure ANOVA or Friedman’s test will be used for the intra-group analysis and either one-way ANOVA or the Kruskal-Wallis test will be used for the inter-group analysis for data with parametric and non-parametric distribution, respectively. The data will be organized and tabulated using the Statistical Package for the Social Sciences (SPSS v.19.0). The level of significance will be set to 5% (p < 0.05).

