### Sample description and characterization

The sample size will be calculated based on the study carried out by Buckon et al. (2004)[15] with results on gait cadence in children with CP (GMFCS Levels I and II) with and without a fixed AFO. For an expected size effect of 17 steps/minute, with a standard deviation of 15 steps/minute and assuming an α risk of 0.05 and an 80% power, the sample was estimated at 12 children per group. Thus, the sample will be composed of 24 male and female children with CP aged four to 12 years**.**

The participants will be recruited and selected for eligibility based on the criteria listed below.

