The modified Ashworth Scale will be used for the classification of hypertonia. This scale consists of Item 1+ and a five-point scoring system ranging from 0 (absence of tonic alteration) to 4. The classification of severity is related to range of motion at which increased resistance to rapid passive movement is detected [27].

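### A Kolmogorov-Smirnov pre-test chooses the summary measure and the tests for every outcome, and at 12 children per arm it is a poor gate whichever version of the test is used

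*Protocol article*

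**What the plan says.** The Statistical analysis section of the protocol article opens with the rule: "The Kolmogorov-Smirnov test will be used to test the data with regard to Gaussian distribution". Three things follow from the result:

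- **Summary measure:** "Central tendency and dispersion measures will be expressed as mean and standard deviation values or median and inter-quartile interval".
- **Within-group test:** repeated-measures ANOVA or Friedman's test.
- **Between-group test:** "either one-way ANOVA or the Kruskal-Wallis test will be used for the inter-group analysis for data with parametric and non-parametric distribution, respectively".

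The section does not say whether the test is corrected for a mean and SD estimated from the sample. It also does not say whether it is run per arm, per visit, on pooled data or on residuals. No outcome is exempt, including the modified Ashworth Scale, which the Instruments section describes as graded: "This scale consists of Item 1+ and a five-point scoring system ranging from 0".

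On size, the Sample description section says "the sample was estimated at 12 children per group", 24 children in all. The abstract and the Procedures section give five evaluation occasions.

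**The concern.** A normality pre-test is useful only if it separates data that suit the parametric method from data that do not. With 12 observations a Kolmogorov-Smirnov test does this poorly, and the failure differs by version. Without correction it hardly ever rejects, so skewed and ordinal data pass to ANOVA by default. With correction it rejects some clearly skewed samples, misses most of them, and flags 5% of truly Gaussian ones.

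What is at stake is whether the analysis is fixed before the data are seen. Under this rule the test, the summary and the kind of effect reported (a difference in means or a comparison of ranks) depend on the sample. One outcome may be reported by means and a similar one by medians. If the check is run at each visit, the same outcome may change method over follow-up. For Ashworth no test is needed at all, because the measurement scale is known in advance.

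**Working it through.** **The plan's own figure.** The design assumption is "For an expected size effect of 17 steps/minute, with a standard deviation of 15 steps/minute", with alpha 0.05 and 80% power. Two-sided alpha is assumed, since the protocol does not state it.

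n per group = 2 × [15 × (1.960 + 0.842) / 17]² = 12.2

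This agrees with the stated 12 to within rounding (13 if rounded up, 14 with the t distribution). So 12 per arm, before any dropout, is the right size at which to judge the gate. The standardised design effect is 17/15 = 1.13.

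**Step 1: how often the gate rejects at n = 12.** Mean and SD are estimated from each sample, at the 5% level. The uncorrected critical values are D = 0.375 (exact) and 0.392 (asymptotic). The Lilliefors value, simulated from 200,000 normal samples, is 0.242. There were 40,000-50,000 samples per distribution. The protocol gives no distributional data, so the shapes are assumptions.

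| Distribution | Uncorrected | Lilliefors |
|---|---|---|
| Normal | about 0.01% or less | 5% |
| Gamma, shape 4 (skewness 1) | under 0.1% | 12% |
| Gamma, shape 2 | under 0.2% | 20% |
| Lognormal, sigma 0.5 | 0.1-0.3% | 21% |
| Exponential | 0.4-0.8% | 36% |
| Lognormal, sigma 1 | 3-5% | 54% |
| Ashworth-like, five grades with probabilities 0.1/0.3/0.3/0.2/0.1 | about 1-1.5% | 48% |

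**Step 2: pooling both arms (n = 24).** Lilliefors rejects 22% (gamma, shape 4), 41% (lognormal, sigma 0.5), 68% (exponential) and 92% (Ashworth-like). The uncorrected test still rejects only 7% or fewer of exponential samples. Pooling therefore improves the corrected test, but it mixes any group difference into the shape being tested.

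**Step 3: false flags across visits.** If one truly Gaussian outcome is tested in each of 2 arms × 5 occasions with Lilliefors:

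- ten independent cells: 1 − 0.95¹⁰ = 40%;
- visits within an arm perfectly dependent: 1 − 0.95² = 10%.

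Repeated measures on the same children should put the true figure between these.

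**Step 4: the two-stage rule in full.** 20,000 two-arm trials of 12 per arm were simulated for each of seven shapes: normal, uniform, t with 3 df, and the gamma (shape 4), exponential and two lognormals above. The rule is Kruskal-Wallis if either arm fails Lilliefors, otherwise ANOVA.

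- *Kruskal-Wallis chosen:* 9% of trials with normal data, 23% with gamma (shape 4), 38% with lognormal (sigma 0.5), 59% with exponential.
- *Type I error, two-stage rule:* 5.1-5.8%.
- *Type I error, one test fixed in advance:* 3.4-5.2% for ANOVA, 5.0-5.3% for Kruskal-Wallis.
- *Type I error within a branch:* 6.8-8.4% for ANOVA after a pass with strongly skewed data; 7-9% for Kruskal-Wallis after a fail with normal or uniform data.
- *ANOVA and Kruskal-Wallis disagree on significance at the design effect:* 6-15% of trials.

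Either test fixed in advance holds the 5% level, so the gate is not needed for error control.

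**The case against.** The best defence is that both branches are named in advance and the overall error rate barely moves. That stands: 5.1-5.8% is not gross inflation. Even if Ashworth grades went to ANOVA, simulated type I error at 12 per arm was 5.0-5.1% for three assumed five-grade distributions.

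A second defence is that the unit of testing and the correction are details that an article may leave to a fuller plan. This also stands in part. The silence is not the finding, and switching between visits or arms arises only if the check is run per cell. But the gate itself is stated, and neither version works well at n = 12.

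Some stronger readings are tempting, and the documents do not support them:

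- *The test cannot detect non-normality at this size.* That fits the uncorrected version. Lilliefors has low power, but still rejects 36% of exponential and 54% of very skewed lognormal samples.
- *The rule both never rejects and lets chance pick the method.* These faults belong to different versions. The uncorrected gate almost never switches, so in effect it means always ANOVA. At most one fault applies.
- *Ashworth grades will be analysed by ANOVA.* That is likely only with the uncorrected test. With Lilliefors the choice is close to even per arm.
- *The rank branch is what loses the baseline value.* One-way ANOVA does not use it either, so the pre-test is not the cause.

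**Conclusion.** The point holds as a weakness in a stated rule and should be corrected. At 12 per arm the gate is either close to no check (uncorrected) or largely a matter of chance (Lilliefors). In both cases no analysis is fixed for any outcome. The practical size is the 6-15% of simulated trials at the design effect in which the choice of branch would change the significance result, together with possible mixing of means and medians across outcomes or visits. A reader might infer a seriously inflated false-positive rate; the simulations do not show one.

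The figures rest on assumed distributions, a 5% pre-test level, testing within arm and no dropout. The Ashworth-like variable has five assumed grades, without the extra 1+ grade. The 40% figure for false flags also needs ten independent cells and is best read as the top of a 10-40% range.

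**What to change.** Delete the normality gate and name one between-group analysis per outcome, chosen by measurement type:

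- **Continuous outcomes (cadence, other gait measures, sway, Up-and-Go, six-minute walk):** a baseline-adjusted linear model. Judge fit on residuals, and give a rank-based or permutation analysis as a sensitivity analysis whatever the residuals show.
- **Modified Ashworth:** an ordinal or rank-based between-group analysis.
- **Summaries:** fix mean and SD, or median and inter-quartile range, by outcome type and keep the same summary at all visits.

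Baseline adjustment goes a step beyond removing the gate, but it uses measurements already scheduled. The cost is a reworded Statistical analysis paragraph and a little more analysis work. The small downside is that robustness is shown by sensitivity analysis instead of a pre-test. Nothing changes in sample size, visits or data collection.

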### Sample composition

After fulfilling the eligibility criteria, the children will be randomly divided into two groups: 1) a control group that will make use of AFOs exclusively and 2) an experimental group that will make use of AFOs combined with posture-control insoles.

Children in therapy at rehabilitation centers will be recruited and instructed to maintain their normal therapy throughout the study. Randomization with involve a series of sealed opaque envelopes to ensure confidentiality. Each envelop will contain a card stipulating to which group the child will be allocated.

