### Procedures

The children selected (whose legal guardians agreed to their participation by signing a statement of informed consent) will be evaluated regarding their anthropometric data and GMFCS classification and randomly allocated to the experimental and control groups. The control group will make daily and constant use of the AFOs. The experimental group will make use of the posture-control insoles for six hours daily during the most active period of the day and will remain using the AFOs the rest of the day.

The evaluation process (before, immediately after, one month after, six months after and one year after insole use) will be performed under two different conditions. Under the first condition (evaluation 1), the children will not use an assistance device and under the second condition (evaluation 2), the children will use either the posture-control insoles or the AFOs, depending on the group to which they belong. Evaluation 1 and evaluation 2 will be performed by different examiners. Examiner 1 will not be aware of which group the children belong, thereby characterizing the investigation as a blind study.

The evaluations will be held on two non-consecutive days. The Berg Balance Scale, Timed Up-and-Go Test, Six-Minute Walk Test and modified Ashworth scale will be administered on the first day. The three-dimensional gait analysis and the static balance test on a pressure plate will be performed on the second day.

For the three-dimensional gait analysis, the equipment will be introduced to the children and the procedures will be explained. The children will be submitted to an initial practice gait exam to become familiarized with the procedure (no data will be collected on this training run). The children will wear bathing suits to facilitate the placement of the markers. The skin will be cleaned with alcohol for better attachment of the markers on the exact sites. The markers will be enveloped in adhesive tape lined with microscopic glass spheres and attached to a plastic base with double-sided adhesive tape. The markers will be attached to the children in the orthostatic position, as suggested by Davis et al. (1991), [28] on the following anatomic structures:

Pelvis: Three markers will be positioned on the anterior superior iliac spines (right and left) and one between the posterior superior iliac spines.

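### The arms are compared only by one-way tests with no baseline covariate and no group-by-visit term, while change over time is tested only within each arm

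*Protocol article*

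**What the plan says.** The Statistical analysis section of the protocol article gives each test a role. Of repeated-measures ANOVA and Friedman's test, one or other "will be used for the intra-group analysis and either one-way ANOVA or the Kruskal-Wallis test will be used for the inter-group analysis", the choice within each pair depending on the distribution of the data. No other comparative analysis is named, so there is no baseline covariate, no change score and no group-by-visit term.

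The design supplies what such an analysis would need. Under Sample composition, "the children will be randomly divided into two groups": AFOs alone, or AFOs with posture-control insoles. Under Procedures, evaluations are set at five occasions ("before, immediately after, one month after, six months after and one year after insole use"), each under two conditions, without a device and with the assigned device.

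The sample size section is based on gait cadence: "For an expected size effect of 17 steps/minute, with a standard deviation of 15 steps/minute", "assuming an α risk of 0.05 and an 80% power", from which "the sample was estimated at 12 children per group".

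**The concern.** The aim in the Introduction is the effect of combining insoles with AFOs, so the answer has to come from comparing the arms. The plan puts time into the within-arm analysis only and leaves the comparison of arms to a test that uses neither the pre-treatment value nor the repeated visits. Two things follow.

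- **Precision.** The children range from four to 12 years, so a one-way comparison of follow-up values carries all the between-child variation. Part of that could be removed with a baseline that is already being measured.
- **Interpretation.** The children keep their usual therapy and grow for a year, so both arms may change. A within-arm test picks up that shared change. Significance in one arm and not in the other says nothing reliable about a difference between arms, yet such a pair of p-values is easily reported as a benefit of the insoles.

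**Working it through.** **Inputs from the protocol.** Difference 17 steps/min; SD 15 steps/min; 12 per arm; alpha 0.05; power 80%; five occasions, one of them before treatment. Sidedness is not stated; two-sided is assumed.

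**Inputs assumed.** The correlation r between baseline and follow-up is not in the document, so a range is shown.

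**Step 1: the plan's own figure.** By the normal approximation, n per arm = 2 × [SD × (1.960 + 0.842) / difference]² = 2 × [15 × 2.802 / 17]² = 12.22. Power at 12 per arm on the same approximation is 79.3%. The stated 12 per arm is reproduced within rounding, so the sample size figure is not the fault here.

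**Step 2: power of the planned between-arm test.** With two groups, one-way ANOVA is the two-sample t-test. The noncentrality is 17 / (15 × √(2/12)) = 2.776, with 22 degrees of freedom, which gives power of 75.6%.

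**Step 3: the same comparison adjusted for baseline.** ANCOVA reduces the residual SD to 15 × √(1 − r²) and uses one more degree of freedom, leaving 21. The noncentrality is 17 / (residual SD × √(2/12)).

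| Assumed r | Residual SD | Noncentrality | Power at 12 per arm |
|---|---|---|---|
| 0.3 | 14.31 | 2.91 | 79% |
| 0.5 | 12.99 | 3.21 | 86% |
| 0.6 | 12.00 | 3.47 | 91% |
| 0.7 | 10.71 | 3.89 | 96% |

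At r = 0 the adjusted power is 75.4% against 75.6%, so the lost degree of freedom costs almost nothing even if the baseline proves uninformative.

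**Step 4: what separate within-arm tests do when the arms do not differ.** Simulation of 3,000 trials per setting: 12 per arm, five visits, SD 15, assumed within-child correlation 0.5, and the same true shift from baseline in both arms at all four later visits. A repeated-measures ANOVA is run in each arm at 5%.

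| Shared true change (steps/min) | One arm significant, the other not |
|---|---|
| 0 | 10% |
| 5 | 29% |
| 8.5 | 49% |
| 10 | 47% |
| 12 | 38% |
| 17 | 4% |

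The treatment difference is zero in every row. Disagreement peaks where each arm has roughly an even chance of reaching significance, and falls once the shared change is large enough for both arms to show it. Other assumed settings (correlation 0.6 to 0.8, gradual improvement reaching 0.4 to 0.6 SD, 4,000 trials each) gave about 25% to 50%.

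**The case against.** The strongest reply is that the plan does contain a randomised comparison. An unadjusted two-group test is unbiased under randomisation and keeps its 5% level at any single visit. That stands: the loss is of precision, not validity.

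Second, the disagreement rates are not an error rate of the plan. They become false claims only if significance in one arm alone is read as a treatment effect, and the protocol nowhere proposes that reading. This also stands. The figures show why the within-arm tests should carry no weight in a treatment claim; they do not show that the trial will make one.

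Third, the protocol does not say whether the one-way test is applied to follow-up values or to change from baseline. If it were applied to change, the variance would be 2(1 − r) × SD², and power at 12 per arm would be 61% at r = 0.3, 75.6% at 0.5 and 93% at 0.7. ANCOVA is higher in each case (79%, 86%, 96%), so the point holds on either reading.

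Fourth, r is unknown, and a no-device baseline may correlate less strongly with a with-device follow-up. At r = 0.3 the gain is only from 75.6% to 79%. That is why the range starts there.

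A reader might also infer that the plan drops every child who misses a visit, because standard repeated-measures ANOVA and Friedman's test need complete rows. The document does not say so. Handling of missing data may be set out elsewhere, and a one-way test at one visit would keep every child who attended it. Nor is it right that the baseline is ignored altogether: it enters the within-arm tests as one of the time points.

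**Conclusion.** The point holds as one of precision and interpretation. The protocol fixes a between-arm analysis that has no baseline covariate and no group-by-visit term, although the question is between arms and the baseline is collected. At the plan's own effect and SD, the planned test has 75.6% power. Baseline adjustment raises this to 79% to 96% for assumed correlations of 0.3 to 0.7 with no additional children. These figures assume a two-sided test, equal SDs, complete data and a single covariate. The within-arm tests cannot establish a treatment difference; under the simulated conditions they disagree in 4% to 49% of trials in which both arms change equally.

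Two stronger readings are not supported: that the one-way comparison is invalid, and that the plan commits itself to deleting children with missed visits.

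**What to change.** Replace the inter-group analysis of each continuous outcome with one baseline-adjusted comparison, chosen in advance from two options:

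- ANCOVA at one named primary visit and one named test condition, with group and the baseline value as terms; or
- a linear mixed model with group, visit, group-by-visit and the baseline value, and a child random effect, including all randomised children with any follow-up. With 24 children the covariance should be kept simple; an unstructured matrix over four follow-ups needs ten variance and covariance parameters.

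In either case:

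- State whether the outcome is the no-device or the with-device evaluation, since both are taken at each occasion, and which condition supplies the baseline.
- Name the primary visit, so that four per-visit tests are not each read at 5%.
- Report the adjusted between-group difference with its 95% confidence interval.
- Keep within-group changes descriptive, and state that they will not support a claim of benefit.

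Ordinal measures such as the modified Ashworth Scale are outside this change.

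The cost is a reworded paragraph and one degree of freedom for the baseline covariate in the ANCOVA, or a few more in the mixed model. No new visits, measurements or children are needed. As a side benefit, the mixed model uses the observed visits of children who miss some.

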**Methods/Design:**

The sample will be composed of 24 children with CP between four and 12 years of age. After the signing of the statement of informed consent, the children will be randomly allocated to two groups: a control group using AFOs alone and an experimental group using both posture-control insoles and AFOs. Evaluations will be performed on five occasions: without any accessory (insoles or AFOs), immediately after, one month after, six months after and one year after AFOs or insole and AFOs use. The evaluation will involve the analysis of gait, static and functional balance, mobility and hypertonia. The three-dimensional assessment of gait will involve the eight-camera SMART-D SMART-D 140® system (BTS Engineering), two Kistler force plates (model 9286BA) and an eight-channel, wireless FREEEMG® electromyography (BTS Engineering). Static balance will be assessed using a Kistler force plate (model 9286BA). Clinical functional balance and mobility will be assessed using the Berg Balance Scale, Timed Up-and-Go Test and Six-Minute Walk Test. The posture-control insoles will be made of ethylene vinyl acetate, with thermal molding for fixation. The fixed orthoses will be made of polypropylene and attached to the ankle region (AFO). The results will be analyzed statistically, with the level significance set to 5% (p < 0.05).

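### The trial is sized on cadence, but no primary outcome, visit or device condition is named, so the stated 5% and 80% do not attach to its conclusion

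*Protocol article*

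**What the plan says.** **Sizing.** Under Sample description and characterization, the calculation rests on an earlier study "with results on gait cadence in children with CP (GMFCS Levels I and II) with and without a fixed AFO". The difference to be detected is 17 steps/minute and the SD is 15. Error rates are given as "assuming an α risk of 0.05 and an 80% power". The result is stated in these words: "the sample was estimated at 12 children per group".

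**Outcomes.** The Abstract states: "The evaluation will involve the analysis of gait, static and functional balance, mobility and hypertonia". The Instruments and Procedures sections fill this in with the Berg Balance Scale, Timed Up-and-Go, Six-Minute Walk, modified Ashworth, force-plate sway with eyes open and closed, and three-dimensional gait analysis with kinetics and EMG. None is ranked above the others. The Introduction states the aim as an effect on functionality, which no single measure defines.

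**Occasions and conditions.** There are five evaluations, from before use to one year. Procedures says they are done under two conditions: without a device, and with the device of the child's group.

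**Analysis.** Statistical analysis assigns repeated-measures ANOVA or Friedman to within-group comparisons and one-way ANOVA or Kruskal-Wallis to between-group comparisons. It then sets a single threshold: "The level of significance will be set to 5% (p < 0.05".

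**The concern.** A sample size calculation of this kind is a statement about one test: one variable, compared between two groups, once, at 5%. The article makes that statement for cadence, yet cadence is absent from the aim, the instruments, the procedures and the analysis. The analysis section applies the same 5% to everything without saying which comparison decides the trial.

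At stake is what a positive result would mean. If no comparison is singled out beforehand, a p-value below 0.05 on any outcome, at any visit, under either condition, can be offered as support for the insoles. The 5% then describes each test separately and not the trial's conclusion. Likewise, the 80% power refers to a comparison that nobody is committed to making.

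**Working it through.** **1. The plan's own figure.** Inputs from Sample description and characterization: difference 17, SD 15, alpha 0.05, power 80%. Sidedness is not stated; two-sided is assumed.

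n per group = 2 × [15 × (1.960 + 0.842) / 17]² = 12.22.

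This is 12 to the nearest whole number and 13 rounded up. With 12 per group, normal-approximation power is Φ(17 / (15 × √(2/12)) − 1.960) = Φ(0.816) = 79.3%. With a t-test it is 75.6%, and 14 per group would be needed for 80%. The stated 12 is thus reproduced, for **one** test of **one** variable at 5%.

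**2. Counting possible between-group tests.** The count uses six measures, allowing only one variable each for gait and static balance: cadence, sway, Berg, Timed Up-and-Go, Six-Minute Walk, Ashworth.

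- One visit, one condition: 6.
- Four post-baseline visits, one condition: 6 × 4 = 24.
- Four post-baseline visits, two conditions: 6 × 4 × 2 = 48.

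The 24 and 48 assume separate testing by visit and by condition. Within-group tests, the second sway condition, and the separate kinematic, kinetic and EMG variables are left out.

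**3. Chance of at least one false positive if no effect exists.** Under independence it is 1 − 0.95^k. With a common correlation ρ it is 1 − ∫ φ(u) [Φ((1.96 − √ρ·u)/√(1−ρ)) − Φ((−1.96 − √ρ·u)/√(1−ρ))]^k du. The documents give no correlations, so ρ is an assumption.

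| Tests | Independent | ρ = 0.5 | ρ = 0.7 |
|---|---|---|---|
| 6 | 26% | 21% | 16% |
| 24 | 71% | 46% | 31% |
| 48 | 91% | 61% | 40% |

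**4. A more structured check.** Two-sample t-tests were simulated with 12 per group (10,000 runs), with separate correlations between outcomes / visits / conditions.

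| Correlations | 6 tests | 24 tests | 48 tests |
|---|---|---|---|
| 0.3 / 0.5 / 0.5 | 25% | 60% | 82% |
| 0.5 / 0.7 / 0.7 | 21% | 48% | 66% |
| 0.7 / 0.8 / 0.8 | 17% | 35% | 49% |
| 0.8 / 0.9 / 0.9 | 14% | 25% | 33% |

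The last row is a very high correlation, and every entry in it is still several times 5%.

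**5. Inferring cadence as primary is not enough.** Four later visits under two conditions leave 4 × 2 = 8 candidate comparisons of cadence alone. If each were tested, 1 − 0.95⁸ = 34% under independence, and the formula in step 3 gives 19% at ρ = 0.7.

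**6. Cost of the alternatives.** These figures assume the same standardized effect, 17/15 = 1.13, for every measure, and t-test power.

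- One named primary test: alpha stays 0.05 and the planned size is unaffected.
- Bonferroni over six measures (alpha 0.05/6 = 0.0083): power at 12 per group is about 47%, and 21 per group are needed for 80%.
- Bonferroni over 24 tests (alpha 0.05/24 = 0.0021): power is about 28%, and 27 per group are needed.

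**The case against.** **Separate testing is not stated.** A reader might infer that every outcome, visit and condition is tested at 5%. The article does not say so. It names types of test and one general level. Change over time is assigned to repeated-measures ANOVA or Friedman, which give one overall test per outcome within each group. The between-group test could be run at one visit, on change scores or at every visit. A one-way test has no time factor, which in a five-visit design points towards visit-by-visit comparisons, but that is an inference. This objection stands: the 24 and 48 are conditional counts.

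**The doubling for condition is uncertain.** Procedures describes two conditions at each evaluation. The Abstract can be read as making the no-accessory assessment simply the first of the five occasions. On that reading the step from 24 to 48 falls away. This also stands.

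**Multiplicity rules may be elsewhere.** An adjustment method or an ordering of secondary outcomes is ordinary SAP content, and its absence from an article is not a fault. That is right, and no such fault is claimed here. The choice of primary outcome is different: it belongs in the protocol, and the sample size depends on it.

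**Cadence is already singled out by the sizing.** It is the only sized outcome, so it could be taken as primary by implication. The article never calls it that, and the implication would still leave visit and condition open (step 5).

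**Cadence may not be the best choice.** The hypothesis concerns functional tasks of locomotion and balance, and the 17 steps/minute comes from AFO versus no AFO, not from adding insoles to AFOs. Naming cadence ties the alpha and power to a test; it does not show that the assumed effect suits this comparison.

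**Conclusion.** The point holds in a limited form. The article sizes the trial on a single between-group test of cadence and then names no primary outcome, deciding visit or deciding condition, while setting one 5% level for all analyses. As written, neither the 5% error rate nor the 80% power attaches to the trial's conclusion. This rests on the text alone and needs no assumption about correlation. The sample size arithmetic is not itself in dispute, apart from rounding 12.22 down.

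The size does rest on assumptions. With six measures it is about 16–26% at one visit and condition, 31–71% over four later visits and 40–91% with both conditions, for common correlations from 0.7 down to independence. At very high correlation it falls to about 14%, 25% and 33%. It would be too strong to say that a false positive is likely: several plausible settings give less than one half, and independence is implausible when the same 24 children are measured repeatedly on related scales. The supported statement is that the risk is well above 5% in every setting examined.

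**What to change.** In the protocol, name cadence, the outcome on which the trial is sized, as the single primary outcome. State one visit and one evaluation condition for it, and test it between groups at two-sided 5%. Classify all other outcomes, visits and conditions as secondary or exploratory and report them as estimates with 95% confidence intervals. Any adjustment among the secondaries, such as Holm, can be left to the SAP. If the sponsor prefers another outcome as primary because it fits the functional aim better, the sample size must be justified again for that outcome.

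The cost is one paragraph and a matching registry update, with no change to the planned 24 children. The downside is that secondary results can no longer carry a confirmatory claim.
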